## Abstract

**Background:**

Given evidence that parenting can influence children’s development, parenting interventions are often the strategy of choice when it comes to treating children’s disruptive behavior problems—or preventing problems from developing in the first place. What remains under appreciated, however, is that some parents appear to be more responsive to interventions to foster skilled parenting than others. Notable in this regard is the ever-increasing observational and, perhaps more importantly, experimental evidence indicating that some children prove more susceptible to parenting interventions than others. So, while the experimental evidence clearly indicates that “susceptibility factors” which children carry seem to affect their likelihood of benefiting from a parenting intervention (and other environmental influences), what remains unclear is why the parenting interventions in question prove more effective in changing the behavior of some parents more than others. Could it be as a result of their own parental characteristics?

**Objective:**

The Parfective Microtrial in a randomized controlled microtrial, in which we focus not just on parental (and child) responsiveness but also on an underlying physiological mechanism hypothesized to contribute to heightened susceptibility to parenting interventions.

**Methods:**

Participants are 120 families, with children aged 4–5 years, recruited from the community. Of these, 60 are randomly assigned to the “micro” intervention condition (i.e., immediate positive parenting feedback) and 60 families to the care-as-usual control condition. Assessments in both conditions will be conducted at baseline (pretest), after 2 weeks (posttest), and after 4 weeks (follow-up). Primary outcomes are the hypothesized moderating effects of physiology on the anticipated “micro” intervention effect (i.e., decrease in negative parenting behavior and/or increase in positive parenting behavior). Secondary outcomes are the observed (changes in) child behavior in response to the parenting intervention, such that those parents and children—in the same family—who manifest these physiological attributes will prove most susceptible to the beneficial effects of the intervention.

**Trial registration:**

This study protocol is registered at ClinicalTrials.gov (NCT05539170).

## Introduction

Parenting is widely regarded as an important *and* modifiable determinant of children’s problem behavior, one which has thus proven responsive to intervention [1]. While intervention effects are small in magnitude, with even the most successful programs proving effective for only 25% of enrolled families [2], it remains under appreciated that some parents appear to be more responsive to interventions to foster skilled parenting than others. Thus, what remains unclear is *why* some parents prove more susceptible to effects of intervention on parenting than do others. Notable in this regard is the ever-increasing observational and, perhaps more importantly, experimental evidence indicating, respectively, that *(a)* some *children* prove more susceptible to (observed) parenting and parenting interventions than others because of their own “biological sensitivity”, be they behavioral/temperamental, physiological, and/or genetic in nature; and *(b)* that intervention responsiveness is especially pronounced when parents themselves evince more rather than less change in their parenting in response to the intervention [3, 4]. What remains unclear is why some parents prove more responsive when it comes to changing their parenting in response to interventions than others. We hypothesize that it is due, at least in part, to their own underlying physiological processes which can be measured with physiological signals (e.g., heart rate, skin conductance) by means of wearable technology.

Given that parenting interventions are often the strategy of choice when it comes to treating disruptive behavior problems in children—or preventing problems from developing in the first place—it is perhaps surprising that no experimental intervention research has focused on differential change in parenting behavior in response to intervention or on underlying biological/physiological processes that might account for parents’ differential response to intervention [5]. Some *observational* evidence does indicate, however, that parents’ biological sensitivity affects the extent to which a variety of contextual conditions influence parenting. Consider in this regard evidence showing that low and high quality levels of environmental context predict, respectively, less and more positive parenting, but specifically in the case of parents carrying select plasticity genes [6, 7]. Such evidence raises the possibility that parents’ own characteristics of biological sensitivity—obtained from physiological signals are also associated with their susceptibility to parenting interventions, a possibility we aim to evaluate by using a randomized controlled microtrial approach. Microtrials are defined as powerful randomized experiments, testing effects of brief environmental manipulations designed to suppress specific risk mechanisms or enhance specific protective mechanisms, but not to bring about full treatment or prevention effects on temporally distal outcomes [8, 9]. More specifically, we will use a “micro” intervention that has been proven effective in fostering parents’ positive parenting and children’s positive behavior, by providing immediate positive feedback about one’s competence as a parent [10, 11].

### Physiological-based differential susceptibility

Within the last decades, the differential susceptibility hypothesis [12], a within-person proposition that stipulates that the same individuals who are most vulnerable to adversity may also benefit most from enriched environments, has received much scientific attention over the past decade. The majority of research on this hypothesis has been conducted on children and the parenting they receive. There is repeated indication that children differ in the extent to which they benefit from improved parenting or suffer from dysfunctional parenting due to their individual characteristics [13, 14]. These individual differences “for better and for worse” are believed to be rooted in certain endogenous, biological factors that include *(a)* genes, *(b)* temperamental characteristics, and most importantly for this study, *(c)* physiological endophenotypes (e.g., heart rate variability and skin conductance) (see for example [15, 16]). So, while the experimental evidence clearly indicates that some *children* are likely to benefit from a parenting intervention (and other environmental influences), what remains unclear is why the parenting interventions in question prove more effective in changing the behavior of some parents more than others. Could it be as a result of *parental* physiological endophenotypes? Quite conceivably, then, some children—based on their own physiological characteristics—might change more in response to change in parents’ positive parenting, which itself is a result of parents’ susceptibility to environmental influence.

Endophenotypes are genetically informed, stable bio-behavioral traits that function as mediators between genes and phenotype [17, 18]. They seem to be of relevance to differential susceptibility research because of their role in sensitizing the individual to their environmental exposures [19, 20]. We speculate that negativity and positivity actually reflect a highly sensitive nervous system on which experience registers powerfully [21]—negatively when not regulated but positively when positive valence is elicited—a point of view somewhat related to that biological-sensitivity-to-context proposal that individuals who are highly physiologically reactive to stress manifest the most developmental plasticity [22]. More specifically, physiological endophenotypic signals such as heart rate (HR) and skin conductance (electrodermal activity, EDA) are increasingly being used in clinical practice and child healthcare research as they provide innovative ways to bring neuroscience from the lab to real-life settings [23–25]. Thus, we will rely on a very promising state-of-the-art strategy but *minimally invasive* approach, which makes it possible to evaluate differential parental/child responsiveness to a brief and effective “micro” parenting intervention. Notable in this regard is evidence that parents’ physiological reactivity could indeed account for greater and lesser responsiveness to intervention effects, in that only fathers with higher physiological reactivity showed increased positive parenting after receiving a parenting intervention designed for military families with school-aged children [26]. This suggests that physiological reactivity may be a biomarker that makes some parents more responsive to intervention effects than others [27].

### Microtrial to detect intervention heterogeneity

Randomized controlled trials (RCTs) of full-scale interventions can provide insight into these questions—that is, they utilize experimental designs that can provide evidence of intervention heterogeneity that complement and extend data from non-experimental investigations. In addition, the experimental feature of these intervention studies can greatly increase their power to detect interaction effects as compared to observational-correlational studies [28]. However, most RCTs have only limited capacity to illuminate why some individuals benefit or provide insight as to what plasticity mechanisms might be productively targeted in individuals who do not benefit. Empirically addressing these issues requires explicit focus on mechanisms through which risk and protective factors might exert their effects, including whether these mechanisms involve biological endophenotypes. Although RCTs of full-scale interventions can provide some insight into these issues, their utility is constrained by the considerable cost and effort required to measure biological processes, and by the complex and multifaceted nature of the interventions employed [9].

By contrast, experimental studies designed as randomized controlled microtrials might be better suited for analyzing specific effects of distinct parenting variables on parenting and child outcomes. Recall that microtrials are based on relatively brief and focused environmental manipulations designed to suppress specific risk mechanisms and/or enhance specific protective mechanisms, but not to bring about full treatment or prevention effects in distal outcomes. In particular, a randomized controlled microtrial can test hypotheses about underlying behavioral processes by examining whether certain mechanisms change in the experimental condition, mediating the intervention effect [8]. Indeed, if the underlying plasticity process can be illuminated in a less expensive microtrial is would provide an empirical basis for moving to more extensive RCTs.

### Hypothesis and aim of the study

The Parfective Microtrial is a randomized controlled microtrial informed by a physiologically-based measurement tool to illuminate determinants of variation in response to a ‘micro” parenting intervention, using a community sample. The study examines not just parental (and child) intervention responsiveness, but also an underlying physiological mechanism thought to contribute to heightened susceptibility to parenting interventions. In so doing, this study addresses a widely-appreciated need when it comes to advancing understanding of why some individuals prove more responsive to intervention efforts—the need to illuminate underlying biological mechanisms that instantiate differential susceptibility to interventions. Moreover, it will be the very first to simultaneously focus on parent susceptibility to the intervention and child susceptibility to change in parenting
induced by the intervention.

The primary aim is to investigate whether positive parenting feedback, based on the “micro” intervention, has more effect on the hypothesized physiologically susceptible subgroup of parents, and to investigate why this may be the case. In what follows, we articulate the empirical basis of each of three distinct hypotheses—on parental self-efficacy beliefs, reported parenting behavior (e.g., rejection and affection) and reported child behavior (child externalizing behavior), as well as on observed parenting behavior (e.g., withdrawal and positive affect) and observed child behavior (e.g., irritability and persistence/enthusiasm)—that we will evaluate before delineating our methodology.

### Research questions/hypotheses

Does the randomized controlled microtrial enhance more positive parenting behavior and reduce more child externalizing behavior in “micro” intervention group compared to control condition?*H1*: *We expect that the “micro” intervention will bring about an increase in parents’ self-perceived competence*, *leading to behavior changes in the participating parents and children*. *We expect that immediate positive parenting feedback*, *central to successful parenting interventions*, *will increase the likelihood that parenting improves following intervention*, *as evidenced by a main effect of the intervention vs*. *control group*.Also, we expect that the intervention effect on parenting behavior is more pronounced when parents increase more rather than less in self-efficacy beliefs.Do differential effects of responsiveness to the randomized microtrial vary as a function of parents’ and children’s physiological reactivity?*H2*: *We expect that some parents will disproportionally benefit from the “micro” intervention based on their physiological reactivity*, *such that those who benefit most will score higher on skin conductance and/or heart rate*, *with the same being true of their children*.Do parents and children who share a high physiological reactivity prove most susceptible to the “micro” parenting intervention?*H3*: *We expect that those parents and children—in the same family****—****who both manifest these physiological attributes will prove most susceptible to the beneficial effects of the intervention*. *That is*, *the greatest improvement in child externalizing behavior will occur when both parent and child score high on physiological reactivity*.

## Materials and methods

### Design

The Parfective Microtrial is a randomized controlled microtrial with a “micro” intervention (i.e., immediate parenting positive feedback) and a control condition that tests physiologically-based differential susceptibility to changes in parenting. Participants are 120 families, with children aged 4–5 years, recruited form a community. Of those families, 60 will be randomly assigned to the “micro” intervention condition and 60 families to the control condition. After enrollment in the microtrial and randomization, the baseline assessment (pretest) will be carried out. The “micro” parenting intervention will be implemented after these baseline assessments. Participants in the care-as-usual control condition receive no immediate positive parenting feedback but will also be taken aside without their child, receiving only the instructions of the experiment. For the intervention condition, we will use an established parental self-efficacy microtrial intervention, which has been found to be effective in fostering parents’ positive parenting (ES = 0.63) and children’s positive behavior (ES = 0.64), by providing *immediate* positive feedback about one’s competence as a parent [10, 11]. Posttest and follow-up assessments will be conducted after 2 weeks and 4 weeks, respectively. The study procedure has been approved by the Ethics Review Board of Tilburg University.

### Recruitment

Based on previous work that demonstrated medium effects (*d*) of the “micro” parenting intervention [10, 11, 29, 30] and a priori power analyses for investigating our hypotheses in a two-sided test at α = .05 and power (1-β) = .80 [31], data will be collected from 120 four-to-six-year-old children and their parents—recruited via flyers, social networks and letters distributed by elementary schools in The Netherlands (Fig 1). Exclusion criteria for the children will be *(a)* psychiatric/neurological disorder (as reported by the parent), *(b)* mental retardation (IQ < 70), *(c)* not mastering the Dutch language, and *(d)* that their child is not living in another household during the weekdays. The sample will be recruited, and all data collection will be carried out by the Lifespan Lab of Developmental Psychology at Tilburg University.

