### Randomization

In this randomized, single-blinded, study on intervention heterogeneity, participants will be blinded to details until the end of the microtrial. Randomization (1:1) will occur through random selection of a participant number, linked to either the intervention or control condition. Participants will give consent prior to randomization (see Ethical clearance).

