### Analyses

The data will be collected anonymously by assigning an ID number. Statistical analysis will involve several steps. First, using independent t-tests and/or alternative non-parametric tests, we will examine as a preliminary analysis whether randomization was successful, comparing baseline levels of demographics, parenting behavior and child externalizing behavior across the intervention and control condition. Possible significant differences at baseline will be used as covariates in analyses [47]. Latent change (LC) models in Mplus [48] will be used to test hypothesis H1-H3 on each dependent variable—parental self-efficacy beliefs, parenting behavior, child externalizing behavior and observed parenting and child behavior [49]. Because change is measured directly through latent difference variables, representing inter-individual differences in models are an excellent approach to examining repeated measures to estimate amount of change across time. In an LC model of parenting behavior and child behavior, behavioral change is cast as a latent variable, thereby separating measurement error. The mean of the latent difference variable is used as measure of mean differences between measurements, one to be predicted by other variables, including experimental condition (i.e., “micro” parenting intervention vs. control) and physiological scores. The Bonferroni correction is used to reduce chances of obtaining false-positive results (type I errors) [50].

### Hypothesis 1

◾ The feature of the LC model which evaluates this hypothesis links the “micro” parenting intervention (vs. control) with intervention responsiveness across pretest, posttest, and follow-up assessments, Specifically, the first model affords evaluation of group differences on the change from pretest to posttest and from posttest to follow-up. The second model affords evaluation of group differences from pretest to follow-up and from posttest to follow-up. Because the “micro” parenting intervention is focused on inducing parental self-efficacy beliefs, presumed to affect parents and children by changing their competence as a parent, we will also evaluate whether intervention effects are more pronounced when parents increase more rather than less in self-efficacy beliefs. We have four outcome measurements: reported and observed parenting change and reported and observed change in child behavior.

### Hypothesis 2

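### The 80% power claimed at α = .05 for all hypotheses is supported only for a main effect, while the primary question is an interaction tested under Bonferroni

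*Protocol article*

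**What the plan says.** - **Sample size (Recruitment).** The number of families is introduced with "Based on previous work that demonstrated medium effects" of the intervention, and with "a priori power analyses for investigating our hypotheses in a two-sided test at α = .05 and power (1-β) = .80". The result is that "data will be collected from 120 four-to-six-year-old children and their parents". No value of d is given.
- **Effect sizes (Design).** Earlier results for this intervention are quoted as "positive parenting (ES = 0.63) and children’s positive behavior (ES = 0.64"). Both compare intervention with control.
- **Allocation (Randomization and Design).** 1:1, hence 60 families per arm.
- **Primary question.** The abstract's Methods state: "Primary outcomes are the hypothesized moderating effects of physiology". The aims section likewise makes a larger effect in physiologically susceptible parents the primary aim.
- **Tests (Research questions; Hypothesis 1 to 3).** The leading part of H1 is a main effect of condition. H2 is condition × physiology, with one model per moderator and then a composite. H3 is condition × parent physiology × child physiology.
- **Multiplicity (Analyses).** "The Bonferroni correction is used to reduce chances of obtaining false-positive results (type I errors"). The number of tests in the family is not given.

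**The concern.** The power sentence claims to cover the hypotheses as a group, but its one stated input is the size of the intervention effect. An interaction is estimated less precisely than a main effect: with a moderator split into halves, the standard error of the difference between the two subgroup effects is twice that of the overall effect. A sample sized for a medium main effect therefore does not carry the same power to H2 or H3. The power is also stated at .05, although the analysis will use a smaller threshold.

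Moderation is the reason for the trial. If H2 is not significant and the report repeats a power of .80, a reader may give that result more weight against physiological susceptibility than the design supports.

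**Working it through.** **Inputs from the document:** 60 per arm, two-sided α = .05, power .80, effect size 0.63 for parenting.

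**Assumptions, because the document gives no figure:** d = 0.50 as one reading of "medium"; Bonferroni divisors of 3 to 5 (Hypothesis 1 counts four outcome measurements, and the Analyses section lists five dependent variables); pre-post correlation r of 0.5 to 0.7; the interaction sizes below.

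**1. The plan's own figure (main effect, no baseline adjustment).** Detectable d = (1.960 + 0.842) × √(2/60) = 2.802 × 0.1826 = 0.51 by the normal approximation, and 0.516 by the noncentral t. At d = 0.52 the noncentral t gives N = 120. So 120 / .80 / .05 is what a two-group main-effect calculation at d of about 0.52 gives. At d = 0.50 the power is 77.5%, which is a near miss.

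**2. H1 at the corrected alpha (noncentral t, 60 per arm).**

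| d | .05 | .05/3 | .05/4 | .05/5 |
|---|---|---|---|---|
| 0.50 | 0.775 | 0.62 | 0.58 | 0.55 |
| 0.63 | 0.93 | 0.85 | 0.82 | 0.80 |

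H1 is adequately powered at the quoted effect size.

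**3. H2, standardised continuous moderator.** With condition coded ±0.5, SE of the interaction slope = 2/√120 = 0.183. Covariance adjustment for the pretest multiplies this by √(1 − r²): 0.158 at r = 0.5 and 0.130 at r = 0.7. The detectable slope is (z for alpha + 0.842) × SE, where z is 1.960 at .05, 2.394 at .05/3 and 2.576 at .05/5. Power at slope b is Φ(b/SE − z).

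| | .05 | .05/3 | .05/5 |
|---|---|---|---|
| Detectable slope, unadjusted | 0.51 | 0.59 | 0.62 |
| Detectable slope, r = 0.5 | 0.44 | 0.51 | 0.54 |
| Detectable slope, r = 0.7 | 0.37 | 0.42 | 0.45 |
| Power at slope 0.25, unadjusted | 0.28 | 0.15 | 0.11 |
| Power at slope 0.25, r = 0.5 | 0.35 | 0.21 | 0.16 |
| Power at slope 0.25, r = 0.7 | 0.48 | 0.32 | 0.26 |

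Slopes are in outcome SD per SD of moderator. A slope of 0.25 around d = 0.50 means an effect of 0.25 at −1 SD and 0.75 at +1 SD. A slope of 0.51 around the same average means roughly no effect at −1 SD and about double at +1 SD.

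**4. H2, moderator split into halves (30 per cell, unadjusted).** SE = √(4/30) = 0.365, and the detectable difference at .05 is 2.802 × 0.365 = 1.02 SD. If the whole effect sits in one half (0 versus 1.0), power is 0.78 at .05 and 0.64 to 0.57 at .05/3 to .05/5. With r of 0.5 to 0.7 the same pattern has 0.88 to 0.97 at .05 and, across .05/5 to .05/3, 0.72 to 0.92.

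**5. H3.** With two standardised, uncorrelated moderators the SE is about the same as in step 3. With two half-splits (15 per cell) it is √(8/15) = 0.730; a three-way contrast of 0.5 then has power 0.10 at .05, and the detectable contrast is 2.802 × 0.730 = 2.05 SD.

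**The case against.** **The main-effect figure is sound.** This stands. The document never says d = 0.50, and 77.5% against 80% is a near miss at an assumed value. A reader might infer that the stated number fails to reproduce even for the main effect; it does not fail, since d of about 0.52 returns it. A reader might also infer that dropout invalidates it. The document gives no loss rate, and an article commonly leaves that allowance to the full protocol.

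**The planned model is not a t-test.** Latent change models use the pretest and separate out measurement error, so unadjusted figures can understate power. This stands, which is why a range is shown. The gain is not guaranteed: with pure change scores at r = 0.5 it vanishes.

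**Moderation may be sharp.** The Introduction cites a study in which only the more reactive fathers improved. If the effect is confined to one half, power is much better (step 4). This stands, so low power for H2 cannot be asserted without naming an interaction size.

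**A fuller power analysis may exist.** The text speaks of analyses in the plural and cites a source that is not at hand. A reader might infer that H2 and H3 were never powered; the article does not show that. What it does show is a stated alpha, power and effect basis that do not match the tests they are said to cover.

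**Scales are listed as primary outcomes.** The Primary outcomes section and Table 1 name questionnaires and observed parenting. These are the variables being moderated, and the abstract and the primary aim still put moderation first.

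**Conclusion.** The concern holds for the scope of the power statement. As printed, .80 at .05 is supported for the H1 main effect at d of about 0.52. It is not supported for H2 or H3, nor at the alpha that Bonferroni will impose. H1 has no shortfall at the quoted effect of 0.63; at d of about 0.5 it would have one after correction.

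For H2, 80% power at .05 needs a change in effect of about 0.51 SD per SD of moderator unadjusted, or 0.44–0.37 for an assumed pre-post correlation of 0.5–0.7. At .05/3 to .05/5 these become 0.59–0.62 unadjusted and 0.42–0.54 adjusted. An assumed slope of 0.25 has 28–48% power at .05 and 11–32% after correction, whereas an effect confined to one half of the sample does far better. The true power for the primary question is therefore undetermined by the document. The mismatch itself does not depend on these assumptions; its size does.

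**What to change.** Keep N = 120 and revise the Recruitment and Analyses text:

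1. Restrict the 80% statement to the H1 main effect and name the d that it assumes.
2. State how many tests form the Bonferroni family, and give power at that alpha.
3. For H2 and H3, state the smallest interaction detectable with 80% power under the planned latent change model, with the moderator coding and the assumed pre-post correlation. The sponsor should compute these from its own model; the figures above are a guide to size, not text to print.
4. Report interaction estimates with confidence intervals, so that a non-significant result is not presented as the outcome of a test with 80% power.

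The cost is a short calculation and some rewording, and a less favourable figure for the primary question. No extra families are needed.
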